### Randomization

All public and non-profit health facilities with pMTCT services in the study region in each country were considered for inclusion. Facilities were excluded if they were more than 20 kilometers from a main transport corridor to ensure frequent contact with the study team. Facilities were also excluded if an ongoing prospective study or similar systems analysis and enhancement technique were being implemented, and if facility managers and/or staff were unwilling to participate in the study. Consent for inclusion in the trial was sought from facility leadership after the randomization process.

A total of 90 health facilities providing pMTCT (30 per country) provided the initial sample frame for this study (Figure 2). Study leadership from each country (including the project Principal Investigator) met in November 2013, in Beira, Mozambique, to define intervention and comparison groups. After removing facilities that did not meet the eligibility criteria, the remaining 55 facilities were ranked by country according to volume of first ANC visits. The top 12 facilities were selected in each country, and split into two groups of six facilities (upper and lower 50%, according to ANC volume). Three facilities from each group were assigned to receive the intervention and three to not receive the intervention in each country (using the random number generator in Excel®), totaling six intervention and six comparison facilities per country (18 intervention and 18 comparison facilities in total).

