### Analysis

The primary analysis approach to assess the impact of the SAIA intervention will rely on paired t-tests comparing the average outcome measures over the 12 months preceding the intervention, compared with the average over the three months directly following the intervention period, for the three study outcomes. As a secondary analysis approach, segmented regression analysis that controls for baseline outcome levels and trend to compare the monthly averages before versus after the intervention will be carried out for all three study outcomes. Change points will include a node at the beginning of the intervention period to reflect the introduction of the intervention; two additional terms will be added to the model at the end of the six-month intervention period to indicate the level change and trend change post intervention. To account for a three-month lag in the impact of the intervention, data from the first three months post initiation of the intervention will be excluded from analysis. Sub-analyses will be carried stratified by country and facility size to assess subgroup effects.

Because facilities will be randomly selected and allocated to intervention and control facilities, we do not expect to perform adjusted analyses. However, descriptive characteristics will be compared between intervention and comparison facilities using student’s *t*-test and chi-square tests to assess potential imbalance between study arms, and subsequent analyses will consider covariates significant in bivariate analysis for inclusion in the final model in a stepwise fashion. In addition, because outcomes are reported as a monthly summary measure at the facility level, no additional procedures will be implemented to control for potential intra-class correlation at the cluster (health facility) level. Autocorrelation will be assessed using the Durbin-Watson statistic, and adjusted for if appropriate.

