### Sample size

Sample size estimates are based on the health facility as the unit of analysis, and were calculated to detect the change in the proportion of HIV-infected pregnant women receiving antiretroviral medicines in pregnancy (arguably the most important endpoint of the study). Using program data from 2009 to 2010, we estimated a mean pre-intervention baseline of 50%, and predicted a mean post-intervention level of 70% for intervention facilities (mean change score = 20%) and 50% for control facilities (mean change score = 0%), and a standard deviation of yearly change scores of 11%. Assuming α = 0.05 and β = 0.80, the sample size is sufficient to detect an 11% and a 20% difference in mean change scores across the three countries and at the country level, respectively (Table 4).

**Table 4 T4:** Sample size and detectable change in study outcomes

**Sample size (Intervention: Control)**	**Detectable alternative in gain scores across intervention and control facilities**
6:6	19.7%
12:12	13.2%
18:18	10.6%

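### Stratified analyses are the plan's only stated route to subgroup effects, with no test of whether the effect differs between countries or between facility-size groups

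*Protocol article*

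**What the plan says.** The Analysis section of the protocol article gives subgroup analysis one sentence: "Sub-analyses will be carried stratified by country and facility size to assess subgroup effects". No interaction or heterogeneity test is named there or elsewhere in the article. The tools named in the same section are the primary analysis, which "will rely on paired t-tests comparing the average outcome measures over the 12 months preceding the intervention" with the average over the three months after it, and a secondary segmented regression.

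The Sample size section states detectable differences in mean change score of 11% and 20% "across the three countries and at the country level, respectively". Table 4 gives 19.7% for 6:6 facilities, 13.2% for 12:12 and 10.6% for 18:18. No figure is given for a difference in effect between countries or between size groups.

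The Randomization section describes allocation within country and within the upper and lower half of antenatal volume, three facilities to each arm per cell. The strata are therefore fixed in advance and balanced by arm.

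**The concern.** An analysis within each stratum asks whether there is an effect in that stratum. Whether the effect differs between strata is another question, and it needs a contrast of the stratum effects with its own standard error. Significance in one stratum and not in another is not evidence of a difference, because the strata are small and each result carries its own sampling error.

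This matters more here than in many trials. The section on study facilities and setting says the three countries were chosen as differing settings, and the Methods section expects the results to apply to programmes in diverse settings. Readers will want to know whether the approach works in one country and not in another. If country-by-country results are all they have, a chance pattern could be taken for a real difference and could steer later scale-up.

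**Working it through.** **Inputs.** The Sample size section gives "a standard deviation of yearly change scores of 11" per cent and a planned difference in mean change of 20 − 0 = 20 points. It also says "Assuming α = 0.05 and β = 0.80", read here as 80% power. Sidedness is not stated; two-sided 5% reproduces Table 4. Each country has 6:6 facilities (Randomization section). I assume that facility size means the volume halves pooled over countries, so 3 × 3 = 9 facilities per arm in each half. I also assume independent strata with the same SD. The SD is given only for the antiretroviral outcome.

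**Table 4 first.** For a two-sample t-test on change scores, detectable difference = 11·√(2/n)·(t₀.₉₇₅ + t₀.₈₀) on 2n − 2 df. This gives 19.73, 13.17 and 10.58 for n = 6, 12 and 18 per arm; the noncentral t gives 19.75, 13.16 and 10.57. The plan states 19.7, 13.2 and 10.6, so its figures are reproduced.

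**Mixed significance under one common effect.** The standard error is 11·√(2/6) = 6.35 points in a country and 11·√(2/9) = 5.19 in a size half. Let p be the power in one stratum. The chance that some strata are significant and some are not is 1 − p³ − (1 − p)³ = 3p(1 − p) for three countries, and 2p(1 − p) for two size halves.

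| Common true effect | p, country | Mixed, 3 countries | p, size half | Mixed, 2 halves |
|---|---|---|---|---|
| 20 points (planned) | 81% | 46% | 95% | 9% |
| 15 points | 57% | 74% | 78% | 35% |
| 10.6 points (18:18 in Table 4) | 33% | 66% | 48% | 50% |
| 0 | 5% | 14% | 5% | 9.5% |

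At 20 points all three countries are significant in 0.81³ = 53% of trials; at 10.6 points, in 3%. For three countries 3p(1 − p) exceeds one half when p lies between 0.211 and 0.789, which is a common effect of about 8.1 to 19.5 points. For two halves 2p(1 − p) never exceeds one half.

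**Sensitivity to the test.** If the paired t-test were run within the intervention arm only (6 or 9 facilities, SD 11 assumed), mixed results would occur in 17% (countries) and 0.6% (halves) of trials at 20 points, and in 75% and 41% at 10.6 points.

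**What an interaction test offers.** Under a common effect it declares a difference in 5% of trials by construction, whatever the size of that effect. Its power follows from the same inputs:

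- Size halves: the SE of the difference in effect is 11·√(4/9) = 7.33 on 36 − 4 = 32 df. The detectable difference at 80% power is about 21.2 points.
- Two countries: the SE is 11·√(4/6) = 8.98 on 36 − 6 = 30 df. The detectable difference is about 26.0 points.
- Three countries, 2-df F test: noncentrality is Σ(effect − mean)² / (11²·2/6), with denominator 40.33. Effects of 20/20/0 give 266.7/40.33 = 6.61 and 58% power. Effects of 20/10/0 give 200/40.33 = 4.96 and 46%. Effects of 20/20/10 give 66.7/40.33 = 1.65 and 18%.

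**The case against.** The strongest reply is that the sentence states stratification and no rule of inference. It does not say that p-values will be compared between strata or that a difference will be claimed from such a comparison. Estimates with intervals would fit the wording, and an analysis plan that is not shown might add an interaction test. A reader might infer that the plan commits itself to judging subgroups by which stratum reaches significance; the text does not support that. What remains is that the article ties stratified analysis to the purpose of assessing subgroup effects and sizes a separate country-level comparison, while its stated method contains no test of a difference. That is a stated choice for which a better one exists, and so more than missing detail.

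A second reply is that subgroup effects may simply mean the effect within each country, which Table 4 addresses at 6:6. That is a fair reading, and stratum estimates serve it. They will still be set side by side, so the limit of that comparison should be stated.

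A third reply is that an interaction test in 36 facilities is weak. The figures above confirm this. It is a reason to state the limit; it does not make stratum-by-stratum results a valid substitute.

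Multiplicity is a separate matter. Five strata by three outcomes make 15 tests, and simulation under no effect gave at least one false positive in 46% to 50% of trials. The fix only partly addresses this: six interaction tests at 5% would still give up to 1 − 0.95⁶ = 26% if independent.

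**Conclusion.** The point holds as a cheap improvement. The stated method for subgroup effects includes no test of whether effects differ, and stratum results alone can mislead, chiefly across countries.

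A reader might go further and expect that stratum results will usually disagree by chance. The plan's figures do not support that. At the planned effect, disagreement across countries falls just short of half, and it exceeds half only for common effects of about 8 to 19.5 points. Across two size halves it is uncommon at the planned effect and cannot exceed half at any effect.

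The figures rest on a two-sample comparison of change scores, an SD of 11 in every stratum and for every outcome, independent strata, and size groups of 9:9. The primary comparison is not affected.

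**What to change.** In a facility-level model of change scores by arm, test arm-by-country (2 df) and arm-by-volume-half (1 df) for each outcome. Report the stratum estimates with confidence intervals, labelled exploratory, and claim a subgroup difference only from the interaction test.

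State the limit in figures: at 80% power the detectable difference is about 21 points between size halves and 26 points between two countries, and the country test has 58% power for effects of 20/20/0 and 18% for 20/20/10. Add that a non-significant interaction does not show that the effects are equal.

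The cost is a few sentences and two model terms, with no new data. It does need a facility-level model that includes arm, because the paired t-tests named as primary do not supply one.

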**Methods:**

This study employs a two-arm, longitudinal cluster randomized trial design. The unit of randomization is the health facility. A total of 90 facilities were identified in Côte d’Ivoire, Kenya and Mozambique (30 per country). A subset was randomly selected and assigned to intervention and comparison arms, stratified by country and service volume, resulting in 18 intervention and 18 comparison facilities across all three countries, with six intervention and six comparison facilities per country. The SAIA intervention will be implemented for six months in the 18 intervention facilities. Primary trial outcomes are designed to assess improvements in the pMTCT service cascade, and include the percentage of pregnant women being tested for HIV at the first antenatal care visit, the percentage of HIV-infected pregnant women receiving adequate prophylaxis or combination antiretroviral therapy in pregnancy, and the percentage of newborns exposed to HIV in pregnancy receiving an HIV diagnosis eight weeks postpartum. The Consolidated Framework for Implementation Research (CFIR) will guide collection and analysis of qualitative data on implementation process.

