### Trial design

This study employs a two-arm, 1:1 cluster randomized trial design to assess the effectiveness of the SAIA intervention. The unit of intervention is the health facility. A total of 36 health facilities are part of the trial, including 18 intervention and 18 comparison facilities (six intervention and six comparison facilities per country).

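### Facilities were randomised within six country-by-volume strata, but the primary test has no stratum or baseline term: a conservative loss of precision that costs almost nothing to avoid

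*Protocol article*

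**What the plan says.** **Design.** The abstract describes allocation as "stratified by country and service volume". The Randomization section gives the detail: eligible facilities were ranked by volume of first ANC visits, the largest 12 in each country were kept and "split into two groups of six facilities (upper and lower 50%, according to ANC volume"), and then "Three facilities from each group were assigned to receive the intervention and three to not receive the intervention in each country". Three countries with two volume groups each make six strata of six facilities, 18 per arm in total.

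**Analysis.** The primary analysis is a paired t-test of the 12-month pre-intervention average against the three-month post-intervention average. On adjustment the section says "Because facilities will be randomly selected and allocated to intervention and control facilities, we do not expect to perform adjusted analyses". It then plans t and chi-square tests of baseline characteristics between arms, after which "subsequent analyses will consider covariates significant in bivariate analysis for inclusion in the final model in a stepwise fashion".

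Two provisions touch on strata and baseline elsewhere in that section. A secondary segmented regression controls for baseline level and trend, and sub-analyses are planned by country and by facility size. Neither puts the stratification factors into the main comparison.

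**Selection.** The abstract says "A subset was randomly selected and assigned to intervention and comparison arms, stratified by country and service volume", and the Analysis section repeats the idea of random selection. The Randomization section says instead: "The top 12 facilities were selected in each country, and split into two groups of six facilities".

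**The concern.** Random allocation is offered as the reason for not adjusting, but it does not justify leaving out the factors on which allocation was stratified. Equal allocation within strata removes between-stratum variation from the difference between arms. An unstratified standard error still counts that variation, so it overstates the uncertainty whenever strata differ in the quantity analysed. The Covariates section lists patient volume, the basis of one stratification factor, among characteristics already found to be associated with pMTCT performance.

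The 12-month baseline is measured in every facility, yet in the primary analysis it enters only by subtraction.

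The fallback for covariates is also poorly fixed. Any imbalance between randomised arms is due to chance, so screening on it and then selecting stepwise leaves the later models unknown until the data are seen.

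At stake are interval width and power for moderate effects with only 36 units, a clear specification of the later models, and an accurate account of which facilities the results represent.

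**Working it through.** **Inputs.** 18 facilities per arm in six strata of 3:3 (Randomization). SD of change scores 11 points, alpha 0.05, 80% power, planned effect 20 points, and detectable differences of 19.7, 13.2 and 10.6 for 6:6, 12:12 and 18:18 (Sample size, Table 4). The share r of change-score variance lying between strata is not given; 0 to 30% is assumed.

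**Step 1: reproduce Table 4.** A two-sided, unstratified two-sample t-test on facility change scores (noncentral t, 2n − 2 df, SD 11) gives 19.75, 13.16 and 10.57, which matches the table. A one-sample paired t-test with n facilities gives 15.8, 9.8 and 7.7, which does not. The figures below therefore refer to the between-arm comparison behind Table 4, not to a before-after test as the Analysis section literally words it.

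**Step 2: standard errors.** With total SD 11:
- True SE of the arm difference = 11 × √(1 − r) × √(2/18).
- Expected unstratified SE = √{(2/18) × [121(1 − r) + 121r × 18/17]}.

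At r = 0.2 the true SE is √(96.8/9) = 3.28. The unstratified SE is √[(96.8 + 25.6)/9] = 3.69, a ratio of 1.12.

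**Step 3: detectable difference with stratum terms.** Residual df are 36 − 6 − 1 = 29. The detectable difference is close to (t₀.₉₇₅,₂₉ + t₀.₈₀,₂₉) × true SE = (2.045 + 0.854) × true SE. At r = 0 this is 2.899 × 3.667 = 10.63; at r = 0.2 it is 2.899 × 3.28 = 9.51.

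**Step 4: size and power.** Simulated with 40,000 runs per scenario, six strata of 3:3 and fixed stratum effects.

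| Assumed r | True SE | Unstratified SE | Size, unstratified | Detectable difference with strata (10.57 without) | Power at 10.6 points, without / with strata |
|---|---|---|---|---|---|
| 0 | 3.67 | 3.67 | 5.1% | 10.63 | 80.0 / 79.7% |
| 10% | 3.48 | 3.68 | 3.8% | 10.08 | 81.2 / 83.8% |
| 20% | 3.28 | 3.69 | 2.9% | 9.51 | 82.1 / 87.6% |
| 30% | 3.07 | 3.70 | 2.0% | 8.89 | 83.6 / 91.5% |

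The stratified test holds about 5% throughout. The 95% interval half-width is t × SE. Without strata it is 2.032 × 3.67 to 3.70, about 7.5 points in every row. With strata it is 2.045 × true SE: about 7.5, 7.1, 6.7 and 6.3 points.

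**Step 5: planned effect.** At 20 points the noncentrality is 20/3.667 = 5.45. Unstratified power is 99.96%. With stratum terms it is 99.95% at r = 0 and higher for larger r.

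**Step 6: baseline as covariate.** If pre and post variances are equal and their correlation is ρ, the variance of the baseline-adjusted estimate relative to the change score is (1 + ρ)/2. From 10.6 points, and ignoring the one df spent:
- ρ = 0.5: 10.6 × √0.75 = 9.2
- ρ = 0.8: 10.6 × √0.90 = 10.1
- ρ = 0.9: 10.6 × √0.95 = 10.3

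The article gives no ρ. Equal variances are doubtful, since a 12-month mean is compared with a three-month mean.

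**Step 7: significance screen.** The Covariates section lists seven characteristics. If they are treated as independent, the chance of at least one imbalance at 0.05 is 1 − 0.95⁷ = 30%. Leaving out patient volume, which the strata largely balance, gives 1 − 0.95⁶ = 26%. In a simulation with eight covariates (1,500 runs per scenario), the stepwise step kept size within 4 to 6%.

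**The case against.** **The primary analysis may already deal with what matters.** Subtracting each facility's own baseline removes stable country and volume differences in level. Stratum terms help only if strata differ in change, and the article gives no between-stratum share. This stands: at a zero share nothing is lost, and large shares would be speculation.

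**A reader might infer that a wrong standard error means unreliable positive findings.** The documents do not support that. Any error makes the standard error too large, so the type I error falls below 5%.

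**A reader might infer that the trial is underpowered.** It is not, for the outcome it was sized on. At the planned 20 points, power is about 99.9% with or without strata.

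**A reader might infer that strata and baseline are ignored altogether.** They are not. Country and size appear in sub-analyses, and the secondary segmented regression controls for baseline level and trend. What is missing is their use in the primary comparison.

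**A reader might infer that stepwise selection drives the headline result.** The primary t-test takes no covariates. The sentence concerns subsequent analyses and a final model, most naturally the regression, and no size inflation was shown. What remains is that those later models depend on the data.

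**A reader might infer that non-random selection undermines the comparison between arms.** It does not. Allocation was random, and the Randomization section reports the selection openly. The wording matters for generalisability only.

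**Conclusion.** The point holds as a matter of efficiency and clear specification. The design is stratified and the primary test is not, and random allocation is no reason for that mismatch.

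Adding stratum terms raises the detectable difference from 10.57 to 10.63 points if strata explain nothing. It lowers it to between 10.1 and 8.9 points if they explain 10 to 30% of change-score variance. Over that range the unstratified standard error is about 6 to 21% too large. These sizes rest on an assumed share and on the two-sample comparison that reproduces Table 4. The further gain from using baseline as a covariate rests on an undocumented correlation and could be small.

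The practical benefit is in interval width, in effects near 10 points, and in the HIV-testing and infant-diagnosis outcomes, for which no power is stated.

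The claim of random selection in the abstract and the Analysis section contradicts the Randomization section and should be corrected whatever is decided on adjustment.

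**What to change.** 1. Make the primary comparison, for each outcome, a facility-level regression of the post-period mean on arm, 12-month baseline mean and the six stratum indicators. Residual df: 36 − 1 − 1 − 6 = 28, against 34 for the two-sample test.
2. Delete the between-arm significance tests as a basis for adjustment, and delete stepwise selection. Describe baseline characteristics by arm, and use the listed covariates in one sensitivity model named in advance.
3. In the abstract and the Analysis section, state that the 12 highest-volume eligible facilities per country were selected and then randomly allocated within strata. Limit the conclusion to such facilities.

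The cost is a change of wording and six residual degrees of freedom. The strata and baseline data are already in the design and the data collection, so nothing new has to be gathered.

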### Study measures

#### Primary study outcomes

The three study outcomes include the proportion of women screened for HIV during their first ANC visit; the proportion of HIV infected women receiving antiretroviral medications during pregnancy (either bi-prophylaxis using AZT or combination antiretroviral therapy); and the proportion of infants born to HIV-infected women screened for HIV at six weeks postpartum (or two months in the case of Côte d’Ivoire, following national norms) (Table 3). These outcome measures were selected because they reflect successful progression through steps in the pMTCT cascade, they are likely sensitive to system-level improvements, and they represent steps that, if changed, would meaningfully alter patterns of HIV transmission or access to maternal and infant HIV care. Furthermore, these measures reflect national pMTCT protocols, and are therefore well understood and available in all three study countries. Data will be collected over 12 months before the intervention, during the six-month intervention, and three months after the intervention in both intervention and comparison facilities (21 time points and 36 measurements per time point).

**Table 3 T3:** pMTCT outcome measures

**Study measure**	**Numerator/Denominator**
1. Uptake of HIV counseling and testing	$\frac{\#\mathrm{women}\;\mathrm{counseled}\;\mathrm{and}\;\mathrm{tested}\;\mathrm{for}\;\mathrm{HIV}\;\mathrm{in}\;\mathrm{their}\;\mathrm{first}\;\mathrm{ANC}\;\mathrm{visit}}{\#\mathrm{first}\;\mathrm{ANC}\;\mathrm{visits}}$
2. Use of appropriate ARVs in pregnancy for prophylaxis or initiation of cART	$\frac{\#\mathrm{HIV}‒\mathrm{infected}\;\mathrm{pregnant}\;\mathrm{women}\;\mathrm{starting}\;\mathrm{AZT}\;\mathrm{prophylaxis}\;\mathrm{or}\;\mathrm{cART}}{\#\mathrm{women}\;\mathrm{testing}\;\mathrm{HIV}‒\mathrm{positive}\;\mathrm{in}\;\mathrm{ANC}\;3\;\mathrm{months}\;\mathrm{previously}}$
3. Infant HIV determination	$\frac{\#\mathrm{infants}<6\;\mathrm{weeks}\;\mathrm{of}\;\mathrm{age}\;\mathrm{receiving}\;a\;\mathrm{PCR}\;\mathrm{test}}{\#\mathrm{women}\;\mathrm{testing}\;\mathrm{HIV}‒\mathrm{positive}\;\mathrm{in}\;\mathrm{ANC}\;5\;\mathrm{months}\;\mathrm{previously}}$

ANC: Antenatal care; ARV: Antiretroviral; AZT: Azidothymidine; cART: combination antiretroviral therapy; HIV: Human immunodeficiency virus; PCR: Polymerase chain reaction.

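### Declining any allowance for facility correlation is justified for one change score per facility, but not for the secondary segmented regression on monthly data

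*Protocol article*

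**What the plan says.** Protocol article, Analysis:

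- The primary analysis is "paired t-tests comparing the average outcome measures over the 12 months preceding the intervention" with the three months after it.
- The secondary analysis, for all three outcomes, is "segmented regression analysis that controls for baseline outcome levels and trend to compare the monthly averages before versus after the intervention". It has a node at the start of the intervention, and level-change and trend-change terms at its end.
- To allow for a lag, "data from the first three months post initiation of the intervention will be excluded from analysis".
- On clustering, "because outcomes are reported as a monthly summary measure at the facility level", the plan concludes that "no additional procedures will be implemented to control for potential intra-class correlation at the cluster (health facility) level".
- On time dependence, "Autocorrelation will be assessed using the Durbin-Watson statistic, and adjusted for if appropriate".

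The data structure is given under Primary study outcomes as "21 time points and 36 measurements per time point". Trial design gives 36 facilities, "including 18 intervention and 18 comparison facilities". The Sample size section takes the facility as the unit of analysis and assumes an SD of yearly change scores of 11%.

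**The concern.** Summarising by month removes the correlation between women seen at the same facility in the same month. It does not remove the correlation between months at the same facility, which share that facility's level and its own change over time. The facility was randomised, so the arm effect has to be judged against how much change varies between facilities. A change score does this automatically. A regression on monthly data does so only if the model or its variance estimate recognises the facility, and the plan declines in advance to do that.

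At stake are the P values and intervals of the secondary analysis. If the primary and secondary analyses disagreed, the reader could not tell a real difference in what they estimate from a faulty standard error.

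**Working it through.** **1. The plan's own figure.** A two-sample t-test on facility change scores (SD 11, two-sided α 0.05, power 0.80, noncentral t) gives detectable differences of 19.75, 13.16 and 10.57 for 6, 12 and 18 facilities per arm. Table 4 has 19.7, 13.2 and 10.6. The figures reproduce, so the sample size does treat the facility as the unit.

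**2. Rows available.** 36 × 21 = 756 facility-months. Removing three months leaves 12 + 3 + 3 = 18 per facility, and 36 × 18 = 648. Averaged by arm, there would be 2 × 18 = 36 points.

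**3. Why the standard error goes wrong.** Let λ be the SD of facility levels, τ the SD of facility-specific change and σ the monthly SD within a facility. The article gives none of these. Take τ = 10 and σ = 11.2, so that τ² + σ²/6 = 100 + 20.9 ≈ 11². For a plain before/after contrast between arms (12 months against 6, no trend):

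- True variance: (2/18)[τ² + σ²(1/12 + 1/6)] = (2/18)(100 + 31.36) = 14.60, SE 3.82.
- Facility fixed effects only: residual variance ≈ σ² + 4τ² × 34/610 = 125.4 + 22.3 = 147.7. Here 4 = 6(2/3)² + 12(1/3)², there are 34 df for facility changes within arms, and 610 = 648 − 36 − 2. Reported SE = √[(2/18)(147.7)(0.25)] = 2.03. The ratio to the truth is 0.53, and the false-positive rate is 2[1 − Φ(1.96 × 0.53)] ≈ 30%.
- Pooled, no facility term: residual variance ≈ λ² + σ² + τ²/3. With λ = 10 this is 258.8, SE 2.68, ratio 0.70, rate about 17%. With λ = 20 it is 558.8, SE 3.94, ratio 1.03, rate about 4%.

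So λ² inflates the reported error although it cancels from a change, while τ² is diluted over months although it does not average out. The two errors pull in opposite directions. With τ = 0 the fixed-effects error is correct.

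**4. Effect of the model terms.** False-positive rates at nominal 5% in null simulations (18 facilities per arm, months 1–12 and 16–21):

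| Terms | Pooled | Facility fixed effects | Arm-mean series |
|---|---|---|---|
| No trend, τ = 10 | 18% (λ = 10), 5% (λ = 20) | 30% | 31% |
| Trend and a post step | 0.3–5% | 7–10% | 6–13% |
| Trend, level and slope change at start, level and trend change at end | 0–3% | 3–4% | 5–6% |

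Without trend, lowering τ to 8 brings the fixed-effects and arm-mean rates to about 13%.

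**5. Wider range of assumptions.** A further set had trend, a level change at the start, and level and trend changes at the end, but no slope change at the start. It used λ from 5 to 20, σ from 8 to 17, and serial correlation 0 or 0.4, with τ² = 121 − 5σ²/12 (for example σ = 8 gives τ = 9.71).

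- Pooled, level change at start: rates 0.1–8.2%, reported SE 0.88–1.81 times the truth and above it in 8 of 11 settings. The 8.2% is at λ = 5, σ = 8.
- Pooled, total change to the post period: rates 0.0–5.1%, SE 0.99–2.06 times the truth.
- After AR(1) correction, start term: 1.6–9.6%.
- Arm-mean series, start term (λ = 10): 6.0–17.9%, highest at σ = 8.
- Facility-clustered standard errors: 4.3–6.4%.
- Two-sample t-test on facility change scores: 4.0–6.0%.

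**The case against.** The strongest objection is about size. A reader might infer that the planned regression will declare false effects about 30% of the time. The documents do not support that: 30% needs a contrast without trend terms, and the plan controls for baseline trend. It also needs τ = 10, which puts 100/121 = 83% of the change-score variance into true differences between facilities. With the fullest reading of the planned terms, fixed effects and arm means are near nominal and pooling is conservative.

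A reader might also infer that some 650–750 facility-months will be treated as independent. The article does not say so. It speaks of monthly averages, and Durbin-Watson is ordinarily a check on a single series, so arm-level series are just as plausible.

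Thirdly, autocorrelation is to be adjusted for if needed, and stable facility levels do appear as within-facility residual correlation. That helps in part, but the rates still ran from 1.6% to 9.6%, because a first-order correction does not represent a facility's own lasting change.

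Finally, nothing here undermines the sample size, and the remark on clustering is sound for facility change scores. These limits stand and lower the weight of the point. They do not rescue the stated reason, which is applied to all analyses and is incorrect for one of them.

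**Conclusion.** The point holds for the secondary segmented regression only. The plan excludes any allowance for facility correlation on a ground that is valid for one value per facility and fails for 18 months per facility. The resulting standard errors are generally wrong, and the direction depends on variance components and a model form that the article does not give. Pooled facility-months mostly give errors that are too large, which can hide a real effect. Fixed effects or arm means can give errors that are too small, with rates of about 6–13% under trend and a post step and up to 17.9% in the least favourable setting tried. A few settings come out near nominal because the two errors offset each other. All sizes rest on assumed λ, τ and σ tied to the single published change-score SD of 11%. Facility-level inference stayed close to nominal in every setting in the wider range. The wording should be corrected, but the primary analysis does not depend on it.

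**What to change.** Limit the statement that no further procedures are needed to the analysis with one change score per facility. For the segmented regression, state that facility-months are modelled, list the terms (including whether the node at the start changes level, slope or both), and choose one of:

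- facility-clustered standard errors with a small-sample correction, for 36 clusters overall and 12 in each country;
- a mixed model with a random facility intercept and a random post-intervention change;
- segment estimates fitted per facility and compared between the 18 and 18 facilities.

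Facility fixed effects alone are not enough, because they leave the facility-specific change out of the error term. The Durbin-Watson check can stay as a supplement.

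The cost is a wording change and a standard analysis option. Intervals may become wider or narrower. The small-sample correction matters most in the country subgroups, where a heavily parameterised mixed model may not fit reliably. No new data are needed.
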